**Fig. 2 Fig2:**
[figure not shown]
Motor activities in the Ability Program. Tablet-delivered motor activities in the Ability Program for the upper and lower arm, the trunk and the cervical spine, conducted by a physiotherapist and reported via video clips

Before starting the program, participant and caregiver dyads are invited at the Memory Clinic to collect the Ability kit. On that occasion, they go through a training session lasting approximately two hours. The training that researchers will provide to participants and their carers will focus both on familiarizing with the technological devices of the kit and on how to use them. After a brief explanation of the functions of the several devices of the kit, researchers will conduct the training with a learning-by-doing experiential approach, scaffolding dyads in the management, from beginning to end, of a sample daily Ability session. The aim is to let patients and their carers get a working knowledge of the technological devices of the kit, meant for them as interfaces enabling their care experience, rather than focusing on abstract explanations on the technologies at hand. The participatory appropriation training starts with the opening of the tablet, the familiarization phase with the dashboard, and proceeds with a sample daily session of cognitive activities. The sample session, specifically devised for training purposes, includes at least one cognitive activity within each type of the different implementation designs developed. By implementation design we mean the different actions (e.g., touching a blank space to let the keyboard appear) that a user needs to do to operationalize his intentions (e.g. write a word in a semantic fluency activity) in order to reach the desidered goal. Dyads are invited to operate by themselves on the tablet and, in case of mistakes, an errorless approach will be adopted, in order to encourage their sense of coherence and to empower self-efficacy beliefs in following the tasks proposed. Then, upon completion of the cognitive session, they will manage the transition back to the dashboard with the opportunity to either watch a video of an adapted motor activity or go to the vital parameters measurement recall session, in order to gain confidence in moving back and forth within the platform. Whatever the route selected on which to do first, they will then be invited to do the other, so as to have the opportunity to manage video watching through the tablet and to try the different vital parameters measurement devices. At the end of the tablet session, researchers will show the dyad the FitBit tracker that the participant will have to wear. They will instruct him to wear it day and night for all the 6 weeks of treatment, providing brief hints on its use. To wrap up all the information shared, researchers will provide dyads with a manual showing screenshots of all the basic tablet procedures within daily sessions and pictures describing in detail how to use, to charge, or to wear the several devices of the kit. Moreover, dyads will be informed that phone contacts are planned during the 6 weeks of intervention, with the opportunity of being called or to call themselves both a Support Service Centre for technical problems (e.g. connectivity) and a neuropsychologist as care manager.

#### Treatment As Usual

The ACG will receive TAU, which, according to IRP, comprises: a) paper and pencil cognitive activities to be performed at home 5 days a week, covering the same domains as the Ability Program (See Table 1), with five levels of difficulty progressively increasing week by week independently from participant’s performance the week before; b) prescription to perform light aerobic motor activity 7 days a week (e.g. walking for 30 min.); c) prescription to measure specific vital parameters according to individual clinical condition.

Before starting the program, the participant and carer dyad are invited at the Memory Clinic to collect the workbook containing paper and pencil cognitive activities and written clinicians’ prescriptions about motor activities and measurement of vital parameters. Researchers will provide the dyad with a brief training including instructions a) on the number of days per week in which to perform the exercises, at the same time encouraging the respect for pause periods; b) on the need to respect the dose of daily rehabilitation activities; c) on how to manage down-motivating drawbacks (especially in case of loss of perceived balance between skills and challenge in cognitive activities).

### Assessment design and outcomes measures

The timeline of the study is illustrated in Fig. 3. Assessments will be done in both groups at baseline (T_0), at the end of intervention, 8 weeks after baseline (T_1), and at follow up, 12 months after baseline (T_2).

**Fig. 3 Fig3:**
[figure not shown]
Timeline of the trial. Timing and duration of the various procedures in the trial design

With respect to participants, we will adopt a multifaceted evaluation approach including cognitive functioning, behavioral, functional and perceived quality of life measures. Moreover we will also assess respective caregivers’ perceived burden and psychological well-being.

Participants’ cognitive functioning will be assessed through an extensive neuropsychological battery including:the Montreal Cognitive Assessment (MoCa; [9]), a sensitive tool for general cognitive level assessment;the Free and Cued Selective Reminding Test (FCSRT Delayed Free Recall (DFR) and Immediate Free Recall (IFR); [16]) for long-term memory evaluation;the Trail Making Test (TMT; [19]) for frontal-executive functionsthe Verbal Fluencies [27] for the assessment of language skills.

Participants’ functional and behavioral levels will be evaluated through the following proxy measures:the Activities of Daily Living Inventory (ADCS/ADL; [17])the Neuropsychiatric Inventory (NPI; [10]).

Both are proxy measures administered to caregivers.

Perceived participants’ quality of life (QoL) will be assessed through:the Dementia Quality of Life Instrument (D-QoL; [4]), a dementia-specific self-report measure recommended by the European consensus on outcome measures for non-pharmacological interventions on dementia [24],the Coping Orientation for Problems Experienced – Brief Version (Brief-COPE; [7]), since coping skills are considered as mediator variables for Quality of Life outcomes.

The evaluation of perceived burden and quality of life in caregivers will be done through:the Psychological Well-Being scale (PWB; [30, 31]);the Positive and Negative Affect Schedule (PANAS; [37, 33]);the Coping Orientation for Problems Experienced – Brief Version (Brief-COPE; [7, 32]);the Caregiver Burden Inventory (CBI; [26]).

Only participants in the Ability program group will be also administered, at the end of the intervention (T_1), the System Usability scale (SUS; [5]), in order to test how the Ability platform’s usability is perceived.

As primary outcome measure we consider the QoL of participants, being a measure of how a disease and its treatment affect a person’s capability to develop everyday activities and play valuable roles in their own life. Improvement in QoL plays a key role for individuals living with cognitive impairment, their family and carers. Secondary outcome measures include specific cognitive functioning such as memory, language and executive functions, being those abilities more compromised in MCI due to AD subjects [1], performance of complex instrumental activities of daily living, behavioral symptoms, and rates of conversion in dementia (see previous section).

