
Nonetheless, the efficiency and efficacy of home-based technology-enhanced continuum of care programs are poorly examined and evidences are controversial. Moreover, functional skills, level of patient engagement at home and psychological well-being are under-investigated despite their being key outcomes of interest [21]. Randomized controlled trials (RCT) are strongly needed to determine the optimal design of home-based treatment protocols and identify their long-term benefits.

The main aim of the proposed trial is to test the performance of a technology-enhanced rehabilitation and telemonitoring program (The Ability Program) to ensure the continuity of care from clinical setting to patient’s home. We will investigate whether MCI and people with early AD participating in the Ability program will show improvements in cognition and quality of life (outcome evaluation; efficacy) and better adherence and engagement in the program (output evaluation; efficiency) with respect to MCI and AD subjects taking part in the TAU.

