### Sample size

According to previous multicenter controlled studies [3, 14], sample size calculation was performed considering that under the assumption of normal distribution of the scores (primary outcomes differences between groups) and considering α level of .05, a sample size of 30 subjects resulted in a power greater than 70% and was therefore considered as adequate for this trial. To avoid loss to follow-up and maximize the follow-up sample, standard procedures (regular phone contacts with participants) will be applied.

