### Statistical analyses

Statistical analyses on outcome measures will be conducted using SPSS. We will look at statistically significant changes in primary and secondary outcome measures from T_0 (start of treatment) to T_1 (end of treatment), i.e. a training effect. Moreover, we will look for a treatment (Ability vs. TAU) effect and at training x treatment interactions. This will be done through a 2-way ANOVA. Post hoc analysis will be applied to compare Ability with TAU. An alpha ≤ 0.05 will be considered significant. Moreover, score modification at T_2 (after 12 months) in both groups will be evaluated by means of regression analyses over time considering previous values at baseline and T_1. Contributing factors that may predict changing in outcomes will be also examined in a multivariate interval regression analysis. Moreover, each outcome will be categorized in three intervals according to the criterion of a clinical improvement/stability/impairment which was set by expert physicians. Given the exploratory nature of the study, a stepwise forward model will be set with an entrance alpha level of 0.10. Model assumptions and goodness of fit were evaluated by means of the proportionality of odds across response categories test and the association between predicted and observed values (Spearman rho). When the proportionality of odds assumption is violated, a generalized logistic regression model will be computed. For each significant model, several representative profiles and their associated probability of a successful treatment will be computed.

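### The primary outcome is a construct with no named score, and none of the three ANOVA effects is named as the primary Ability versus TAU test

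*Protocol article*

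**What the plan says.** - **Primary outcome** (Assessment design and outcomes measures): "As primary outcome measure we consider the QoL of participants". The sentence is singular, but it names a construct and no instrument, subscale or total.
- **Instruments for that construct** (same section): two are listed under participants' perceived quality of life. One is "the Dementia Quality of Life Instrument (D-QoL; [4]), a dementia-specific self-report measure recommended by the European consensus on outcome measures". The other is Brief-COPE, included "since coping skills are considered as mediator variables for Quality of Life outcomes".
- **Sample size**: the normality assumption is placed on "primary outcomes differences between groups", in the plural. The power statement is that "considering α level of .05, a sample size of 30 subjects resulted in a power greater than 70" percent. No effect size or standard deviation is given.
- **Statistical analyses**: "We will look at statistically significant changes in primary and secondary outcome measures from T_0 (start of treatment) to T_1 (end of treatment"); the article calls this the training effect. A treatment effect and a training by treatment interaction come from the same 2-way ANOVA, followed by a post hoc comparison of Ability with TAU. The threshold is given once: "An alpha ≤ 0.05 will be considered significant". The 12-month scores (T2) are handled afterwards in a separate regression.

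**The concern.** A reader who follows the text cannot say in advance which single number decides the trial. Two choices are open.

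1. **The variable.** Brief-COPE measures coping. The plan presumes that coping lies on the path to quality of life, yet lists the scale among the measures of quality of life. A shift in coping style could then be reported as a primary quality-of-life result.
2. **The test.** The three ANOVA effects answer different questions, and only one matches the comparative aim. A significant training effect, or a treatment main effect that partly reflects baseline imbalance, could be presented as the primary finding.

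With 15 participants per arm, chance imbalance and shared improvement over time are both likely, so the choice of effect matters in practice.

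**Working it through.** **1. The plan's own figure.** Power above 70% with 30 participants cannot be reproduced, because no effect size or SD is stated. It can be solved backwards. For 15 per arm and two-sided 0.05 (sidedness is not stated, so this is an assumption), power ≈ Φ(d·√(15/2) − 1.960). Setting this to 0.70 gives d = 0.907, since 0.907 × 2.739 − 1.960 = 0.524 and Φ(0.524) = 0.70. The t-based value is d = 0.94. One-sided, d is 0.79 (normal) or 0.81 (t). The calculation has room for one between-arm test at 0.05.

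**2. What each ANOVA effect estimates.** Read the 2-way ANOVA as group (Ability, TAU) by time (T0, T1). Let both arms start at μ, let both gain τ, and let Ability gain a further δ by T1.
- Training effect: the mean change over both arms, τ + δ/2. It is non-zero when δ = 0 if both arms improve.
- Treatment main effect: the difference between arms in the average of T0 and T1, (0 + δ)/2 = δ/2. It halves the effect and carries any baseline imbalance.
- Interaction: the difference between arms in change, (τ + δ) − τ = δ. Only this one is the Ability versus TAU effect.

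**3. Error rate under independence.** With k tests at 0.05 and no true effect, P(at least one significant) = 1 − 0.95^k.
- k = 2 (two instruments, one effect): 1 − 0.9025 = 9.8%
- k = 3 (one instrument, three effects): 1 − 0.8574 = 14.3%
- k = 4 (two instruments, treatment and interaction): 1 − 0.8145 = 18.5%
- k = 6 (two instruments, three effects): 1 − 0.7351 = 26.5%

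**4. Simulation with correlated scores.** Settings: 15 per arm, 20,000 trials per setting, assumed T0-T1 correlation 0.6, assumed correlation between instruments 0, 0.3, 0.5 or 0.8, each test at 0.05. The post hoc comparison is not counted.

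| What may count as primary | No effect of any kind | Both arms gain 0.3 SD, no difference between arms |
|---|---|---|
| One instrument, interaction only | about 5% | about 5% |
| Two instruments, interaction only | 8-10% | 8-10% |
| Two instruments, treatment and interaction | 15-19% | 15-18% |
| One instrument, three effects | about 14% | about 48% |
| Two instruments, three effects | 21-27% | 60-73% |

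A common gain does not affect the interaction test. Over all simulated settings, including a common gain of 0.5 SD, its two-instrument rate ran from 7.5% to 10%. The 48% and 60-73% are not type I error rates, because the gain over time is real. They show how often a significant result would be available that says nothing about Ability against TAU.

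**5. Cost of keeping both instruments.** Testing each at 0.025 with d = 0.907: 2.484 − 2.241 = 0.243 and Φ(0.243) = 0.596. Power falls from 70% to about 60% (59% by t). Restoring 70% needs 2 × (2.241 + 0.524)² / 0.907² = 18.6, so 19 per arm.

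**The case against.** **D-QoL is the natural reading.** The primary sentence is singular, D-QoL is introduced as a recommended outcome measure, and calling coping a mediator of quality-of-life outcomes implies that it is not itself the outcome. This is a fair reading, and the documents do not establish Brief-COPE as a co-primary endpoint. They do list it under quality of life, so the wording leaves the matter open. On the D-QoL-only reading, the three effects still give about 14%.

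**Multiplicity handling may be in a plan not shown.** That stands: the absence of an adjustment is not the point here, and testing each effect at 0.05 is an inference from a single stated threshold. Which variable and which contrast are primary is a protocol matter, and this text fixes it ambiguously.

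**The study is called exploratory.** The word is used to justify the stepwise entry level of 0.10. It does not withdraw the primary outcome or the power statement.

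**The plan already points to a between-arm comparison.** The Sample size section refers to differences between groups, and a post hoc Ability versus TAU comparison is listed. This shows the intent, but it does not single out one of the three effects.

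A reader might also infer more than the text supports:
- *That T1 and T2 compete as primary visits.* The ANOVA is tied to T0-T1, and T2 follows in a separate regression.
- *That the status of cognition is contradictory.* The Background says participants "will show improvements in cognition and quality of life (outcome evaluation; efficacy"), but the outcomes section then ranks quality of life as primary and cognition as secondary. A broad aim followed by an explicit ranking is normal.
- *That the error rate is far larger.* Adding five cognitive scores to the two instruments gives 1 − 0.95^7 = 30%, and 13 scores by three effects gives 1 − 0.95^39 = 86%. These counts include secondary and caregiver scores, which are not routes to the primary claim.

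**Conclusion.** The point holds for the primary variable and the primary contrast. Followed as written, the plan could count a coping score, a pooled change over time, or a group effect averaged over the baseline as a primary result.

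The size depends on which reading is taken: 5% if D-QoL and the interaction are meant, about 14% for D-QoL across three effects, about 7.5-10% for two instruments on the interaction, and about 21-27% for two instruments across three effects. These figures assume unadjusted two-sided tests at 0.05, a T0-T1 correlation of 0.6, and a correlation between instruments of 0 to 0.8. None of these correlations is in the document.

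This should be fixed before analysis, but it does not invalidate the design. The intended primary analysis can be recovered with few words, and the data for it are already being collected.

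**What to change.** - **Assessment design and outcomes measures:** state that the primary outcome is a specified D-QoL score (name the total or subscale) at T1. Describe participant Brief-COPE as an explanatory or mediator variable.
- **Statistical analyses:** state that the single primary test is the Ability versus TAU difference in that score at T1, adjusted for baseline D-QoL, at two-sided 0.05. The T0-T1 group by time interaction serves the same purpose and controls error equally well. The adjusted form is usually more precise: at an assumed correlation of 0.6 its residual variance is 1 − 0.6² = 0.64 of the score variance, against 2 × (1 − 0.6) = 0.80 for change scores.
- Label the training effect, the treatment main effect, the post hoc comparison, all other outcomes and the T2 analysis as secondary.
- **Sample size:** make "primary outcomes differences between groups" refer to the one primary outcome.

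**Cost:** no new data, and no loss of the planned power, which allowed for one test at 0.05. The trial is ongoing, so the change needs a dated amendment. It also leaves fewer routes to a positive claim. Keeping both instruments as primary with a split alpha would be dearer: power of about 60%, or about 38 participants in place of 30, at the back-solved effect size.

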### Statistical analyses

Statistical analyses on outcome measures will be conducted using SPSS. We will look at statistically significant changes in primary and secondary outcome measures from T_0 (start of treatment) to T_1 (end of treatment), i.e. a training effect. Moreover, we will look for a treatment (Ability vs. TAU) effect and at training x treatment interactions. This will be done through a 2-way ANOVA. Post hoc analysis will be applied to compare Ability with TAU. An alpha ≤ 0.05 will be considered significant. Moreover, score modification at T_2 (after 12 months) in both groups will be evaluated by means of regression analyses over time considering previous values at baseline and T_1. Contributing factors that may predict changing in outcomes will be also examined in a multivariate interval regression analysis. Moreover, each outcome will be categorized in three intervals according to the criterion of a clinical improvement/stability/impairment which was set by expert physicians. Given the exploratory nature of the study, a stepwise forward model will be set with an entrance alpha level of 0.10. Model assumptions and goodness of fit were evaluated by means of the proportionality of odds across response categories test and the association between predicted and observed values (Spearman rho). When the proportionality of odds assumption is violated, a generalized logistic regression model will be computed. For each significant model, several representative profiles and their associated probability of a successful treatment will be computed.

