#### Tablet-based cognitive and motor activities in the Ability program

Tablet-based cognitive activities aim to reinforce multiple cognitive domains: attention, reasoning, procedural, semantic and autobiographic memory, executive functions, and visual-spatial skills (see Table 1). Activities within each cognitive daily session are sequentially framed in a way that they typically begin with a learning phase in which several stimuli are proposed. Then, they typically continue with activities that stimulate attention and other cognitive functions. Finally, a recall task is proposed. Each activity is structured into five levels of difficulty that adaptively increase on the basis of subject’s performance. The total time predicted for each daily cognitive session is about 20 min.

**Table 1 Tab1:** Tablet-based cognitive activities

Main domain	Activities: examples of contents
Language	Reading and comprehension of a piece of newspaper article
	Word production from semantic category in a specific time
	Word production based on a specific letter
	Word production based on a specific syllable
	Word production from a semantic category, based on a specific letter
Memory	Recall of popular songs, films or actor’s biographies
	Memorization of daily life notes or brief messages and recall at the end of the cognitive session
	Memorization of a list of words and recall, searching for words which were not included in the list previously stored
	Recall of information in the newspaper article previously read and answering questions about it
	Carefully looking at a painting and memorizing
	Recall of information from a painting previously observed and answering some questions
	Inclusion of correct missing words in the text of some popular poems
Executive function	Putting things in the correct sequence based on a specific criterion
	Putting actions of daily life in the correct sequence
	Mathematical calculations
	Anagrams
	Rebuses (using pictures for words)
	Labyrinths
	Placing hands in empty clocks based on the time indicated in arabic figures
Attention	Finding specific words in a grid of mixed words
	Finding a specific letter in a grid of mixed letters

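### The T0–T1 ANOVA tests three terms without naming the one that decides efficacy; the term labelled as the treatment effect recovers only half the T1 difference, and ANCOVA on baseline would be a better primary test

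*Protocol article*

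**What the plan says.** The Statistical analyses section of the protocol article plans three things for T0 and T1 on the primary and secondary outcomes.

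- A change over time, described as running "from T_0 (start of treatment) to T_1 (end of treatment), i.e. a training effect".
- Two further terms from the same model: "we will look for a treatment (Ability vs. TAU) effect and at training x treatment interactions. This will be done through a 2-way ANOVA".
- A further step: "Post hoc analysis will be applied to compare Ability with TAU".

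The threshold is common to all of them: "An alpha ≤ 0.05 will be considered significant". The section does not say which term answers the trial's question. Nor does it say whether time is a repeated factor.

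Other sections fix the context. The Background states the aim as a comparison with participants receiving TAU. Randomization and masking places randomisation after the baseline assessment. Assessment design and outcomes measures makes participants' quality of life the primary outcome. Both arms follow a six-week cognitive and motor programme. Earlier scores are brought into a regression for the 12-month T2 analysis, but not for T0 to T1.

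**The concern.** The trial asks whether Ability does better than TAU. Three model terms and a post hoc comparison are offered, all judged at 0.05, and they do not answer that question equally well.

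- **Treatment main effect.** This is the term that carries the Ability versus TAU label. It averages a score that treatment cannot have affected (T0) with one that it can (T1). It is therefore diluted and picks up chance baseline imbalance.
- **Time term.** It pools both arms. Both are trained and none is untreated, so practice, regression to the mean and natural course are all in it.
- **Interaction.** This is the between-arm difference in change and does answer the question, but nothing marks it as the deciding test.

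Two things are at stake. The first is the error rate, if more than one term can be taken as success. The second is power, which a trial of 30 people can ill afford to lose when the baseline score is already collected.

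**Working it through.** **Inputs from the protocol article.** There are 30 participants allocated 1:1, so 15 per arm. T0 precedes randomisation. The sample size was set "considering α level of .05", and the article reports that "a sample size of 30 subjects resulted in a power greater than 70" per cent.

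**Inputs assumed, because the article does not give them.** Scores are normal with SD 1 at both times. The true difference at T1 is d = 0.8 SD. The T0–T1 correlation ρ runs from 0.3 to 0.8. Tests are two-sided at 0.05, and all 30 participants contribute T1.

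**The plan's own power figure.** It cannot be reproduced, because no effect size, SD or sidedness is stated. Working backwards, 70% power with 15 per arm needs (1.960 + 0.524) × √(2/15) = 2.484 × 0.365 = 0.91 SD by the normal approximation, or 0.94 SD by the t distribution.

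**What each term estimates.** The standard error of each is its SD below times √(2/15).

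- Treatment main effect: expected (0 + d)/2 = d/2; SD √((1+ρ)/2).
- Interaction (difference in change): expected d; SD √(2(1−ρ)).
- ANCOVA on T1 with T0 as covariate: expected d; SD √(1−ρ²).

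The ratio of ANCOVA to interaction variance is (1−ρ²)/(2(1−ρ)) = (1+ρ)/2. That gives 0.65, 0.75, 0.85 and 0.90 at ρ = 0.3, 0.5, 0.7 and 0.8.

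**Worked case, ρ = 0.5, normal approximation.**

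- Main effect: 0.4/(0.866 × 0.365) = 1.26, power 24%.
- Interaction: 0.8/(1.000 × 0.365) = 2.19, power 59%.
- ANCOVA: 0.8/(0.866 × 0.365) = 2.53, power 72%.

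**Simulation with t-based tests** (20,000 trials per setting, d = 0.8, time as a repeated factor). These are the figures used in the conclusion.

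| ρ | Main effect | Interaction | ANCOVA | Gain, ANCOVA over interaction |
|---|---|---|---|---|
| 0.3 | 26.0% | 43.3% | 58.5% | 15.2 points |
| 0.5 | 23.3% | 56.2% | 67.1% | 10.9 points |
| 0.7 | 20.7% | 78.3% | 82.8% | 4.5 points |
| 0.8 | 20.0% | 91.7% | 92.9% | 1.2 points |

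The mean estimate is about 0.40 for the main effect and about 0.80 for both the interaction and ANCOVA. With no true effect, each of the three rejects in about 5% of trials.

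**More than one route to success.** With equal variances at T0 and T1, a person's sum and difference of scores are uncorrelated, so the main-effect and interaction tests are close to independent under the null. Counting either as success gives about 1 − 0.95² = 9.75%, or roughly 10%.

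**Time term.** With no difference between arms and an assumed common shift of 0.5 SD, it is significant in 61%, 75%, 93% and 99% of trials at ρ = 0.3, 0.5, 0.7 and 0.8. It carries no information on Ability versus TAU.

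**The case against.** The strongest reply is that the planned model already contains the right test. The sentence that introduces the treatment effect also names the training x treatment interaction. In a repeated-measures model that term is unbiased under randomisation and holds its 5% level. This stands. A reader might infer that the ANOVA does not address the between-arm effect at all, and the article does not support that. ANCOVA is the more efficient choice, not the correction of an invalid one, and at high correlation the gain is small.

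A reader might also take the 2-way ANOVA literally, with a person's T0 and T1 scores as independent rows. Simulated error would then be about 8% to 15% for the main effect and 0% to 2% for the interaction. The article speaks of change from T0 to T1, which points to a within-person comparison. A condensed article commonly leaves the model specification to the full protocol or analysis plan. Those rates are therefore not part of this point.

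Three further criticisms carry little weight.

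- **Post hoc step.** It is not empty because there are only two arms. A two-by-two layout has four cells, and comparing the arms at T1 is an ordinary follow-up. The fault is only that it offers another undesignated route to the same claim.
- **The training-effect label.** The article never says that the time term proves Ability's efficacy.
- **Verbal fluency.** Table 1 includes tasks such as "Word production from semantic category in a specific time", and verbal fluency is an outcome. But TAU covers the same domains, fluency is not primary, and the choice of model does not alter the issue.

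What the reply does not meet is that the term labelled as the treatment effect is the diluted one, and that no term is designated as decisive.

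**Conclusion.** The point holds in limited form. The halving of the treatment main effect follows from the design and needs no assumption about effect size or correlation. Its power of 20% to 26% does rest on an assumed 0.8 SD effect. The time term cannot show efficacy against TAU. The false-positive rate of about 10% applies if either the main effect or the interaction may be claimed; it does not apply if the interaction alone decides. The advantage of ANCOVA over the interaction is about 11, 5 and 1 percentage points at correlations of 0.5, 0.7 and 0.8. It depends on assumed values that the article does not supply. The plan contains a valid between-arm test; what it lacks is a statement that this test decides, and it passes over a more efficient one that uses data already collected.

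**What to change.** Replace the ANOVA and post hoc sentences in Statistical analyses with wording such as: the primary analysis compares Ability with TAU on participant quality of life at T1 by ANCOVA with the T0 score as covariate, reporting the adjusted difference with its 95% confidence interval at two-sided alpha 0.05; the same model is used for the continuous secondary outcomes. Name the quality-of-life score in that sentence.

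State that the ANOVA treatment main effect, the time term and any separate post hoc comparison are not tests of efficacy. Report T0 to T1 change within each arm descriptively.

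If the ANOVA is kept, state that time is a repeated factor and that the interaction is the only efficacy test.

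The cost is wording only: no new data and no change to sample size or visits. The downside is the loss of within-group significance claims.
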